## Abstract

**Background:**

Increasing moderate to vigorous physical activity among urban girls of low socioeconomic status is both a challenge and a public health priority. Physical activity interventions targeting exclusively girls remain limited, and maintenance of moderate to vigorous physical activity during the post-intervention period has been difficult to maintain. The main aim of the 5-year “Girls on the Move” group randomized trial is to evaluate the efficacy of a comprehensive school-based intervention in increasing girls’ minutes of moderate to vigorous physical activity and improving cardiovascular fitness, body mass index, and percent body fat immediately post-intervention (after 17 weeks) and at 9-month post-intervention follow-up (9 months after end of intervention).

**Methods/Design:**

A total of 24 urban middle schools in the Midwestern U.S. will be randomized to either receive the intervention or serve as a control (N = 1200 girls). The intervention, based on the Health Promotion Model and Self-Determination Theory, will include: (1) two face-to-face motivational, individually tailored counseling sessions with a registered nurse, one at the beginning and the other at the end of the intervention period; (2) an interactive Internet-based session during which each girl receives individually tailored motivational and feedback messages via iPad at 11 weeks (shortly after midpoint of intervention); and (3) a 90-minute after-school physical activity club. Racially diverse, low-active, 10- to 14-year-old 5^th^ to 8^th^-grade girls will complete questionnaires and physical measures at baseline and post-intervention (n = 50 per school). Minutes of moderate to vigorous physical activity will be assessed with accelerometers. Cardiovascular fitness will be assessed by estimating VO_2_ max with PACER (Progressive Aerobic Cardiovascular Endurance Run) scores. Height and weight will be assessed to calculate body mass index. Percent body fat will be estimated with a foot-to-foot bioelectric impedance scale. Linear mixed effects regression analyses will be performed to assess intervention effects.

**Discussion:**

This multi-component approach is expected to improve girls’ moderate to vigorous physical activity and related physical outcomes.

**Trial Registration:**

ClinicalTrials.gov Identifier NCT01503333

## Background

By 9^th^-grade, only about 22% of girls meet national recommendations of at least 60 minutes of physical activity (PA) every day, and almost 28% are already overweight or obese [1]. An estimated 49% of overweight adolescents and 61% of obese adolescents, ages 12 – 19, have at least one cardiovascular disease (CV) risk factor in addition to their weight status. Among those having a normal weight, approximately 37% have at least one CV disease risk factor [2]. These findings indicate that all girls, regardless of weight status, would benefit from involvement in health-promoting programs, such as those designed to increase PA.

A decline in PA with advancing age across adolescence [3] is related to increases in girls’ body mass index (BMI) and adiposity [4-7]. Girls who are overweight or obese in adolescence are at an increased risk for co-morbidities in adulthood [8,9] and premature mortality [10]. An urgent need exists to intervene before high school is reached to help girls establish a pattern of attaining adequate daily PA as a means to reduce their risk for these adverse health outcomes. Our intervention is directed toward increasing moderate to vigorous physical activity (MVPA) among girls in 5^th^ through 8^th^ grade. Because declining PA is particularly evident among urban, minority girls of low socioeconomic status (SES) [11,12] and increasing their MVPA is a vital public health priority [13], we chose to focus our intervention on this group.

Our intervention extends beyond prior approaches by including two evidence-based strategies offered during or after the school day: Internet-delivered individually tailored counseling and face-to-face motivational interviewing from a registered nurse. Prior studies have used either computerized individually tailored advice [14-17] or motivational interviewing alone [18,19] to increase MVPA among adolescents with limited success. However, Internet-delivered approaches appeal to this age and those that are motivational, theory-based, and individually tailored hold promise as a means for increasing MVPA [20]. Some face-to-face communication is recommended because of its intimacy and rapport [21] and the inherent ability to address individual motivational and emotional factors and barriers not detectable via questionnaires. To our knowledge, no other intervention has directly involved nurses in providing motivational interviewing to promote MVPA among girls, even though nurse-delivered motivational interviewing during school hours has been found to be effective for improving other adolescent behaviors (e.g., reducing smoking) [22,23]. In addition to these two strategies, the intervention provides opportunities for PA (e.g., PA club) after school three days per week with bus transportation home. Because of the integration of these recommended, albeit diverse, strategies and the potential for a synergistic effect, our multi-component intervention is both novel and potentially potent.

### Aims and hypotheses

The main study aim is to evaluate the efficacy of our comprehensive 17-week school-based intervention in increasing girls’ minutes of MVPA and improving CV fitness, BMI, and percent body fat immediately post-intervention (after 17 weeks) and at 9-month post-intervention follow-up (F/U; 9 months after end of intervention). The primary outcome is minutes of MVPA measured after 17 weeks. The intervention includes three components, two of which are individual-level: 1) two face-to-face motivational, individually tailored counseling sessions with a registered nurse, and 2) an interactive Internet-based session during which each girl receives individually tailored motivational and feedback messages (11 weeks). One group-level component, a PA club led by PA instructors (e.g., individuals from community who have experience conducting youth physical activity programs; teachers, including physical education; and sports team coaches), provides an important venue after school to assist girls in establishing a behavioral pattern of MVPA. Girls receiving the intervention will be compared to those in control schools having usual school offerings, some of which may include physical education.

Specific hypotheses include:

•Immediately post-intervention, minutes of MVPA (measured by accelerometer) will be greater by 16 minutes/week among girls in intervention, as compared to control, schools.

•At 9-month post-intervention F/U, minutes of MVPA will be greater among girls in the intervention than control schools.

•Immediately post-intervention and at 9-month post-intervention F/U, CV fitness will be higher and BMI and percent body fat will be significantly lower among girls in the intervention than control schools.

A secondary objective is to examine if MVPA changes are mediated by cognitive (e.g., perceived benefits of PA, barriers to PA, PA self-efficacy, social support) and affective variables (e.g., enjoyment of and motivation for PA).

## Methods/Design

### Study design

The Girls on the Move intervention is a group randomized trial involving 24 racially diverse, urban schools in low SES areas in the Midwestern U.S. In years 2, 3, and 4 of the 5-year study (2011–2016), 8 schools will be randomly assigned to either receive the intervention (n = 4/year) or serve as the control condition (n = 4/year). The research will be reported in accordance with Consolidated Standards of Reporting Trials (CONSORT) recommendations [24].

In order for their school to be included in the study, school administrators must be willing to accept the randomization status of the school and sign a memorandum of understanding. Schools will be included in the study based on the following criteria: (1) location in urban community setting; (2) enrollment greater than 100 girls in each school or more than double the number of girls needed for the study site (n = 50 per school) in any combination of 5^th^, 6^th^, 7^th^, and/or 8th-grade; and (3) student body comprised of at least 50% minority versus non-minority race or ethnicity and including a similar percentage enrolled in the free and reduced lunch program. Schools were excluded if administrators were not interested in participating, did not agree to random assignment, or could not guarantee their availability at 9-month post-intervention F/U.

To avoid any bias, schools are paired prior to randomization based on the following criteria: school type (e.g., academic grades offered), school size, percentage of students who are white vs. non-white race, and proportion of students receiving the free and reduced lunch. Prior to the start of the school year, the PI and project manager inform each principal regarding the randomization status of his or her respective school to assist each principal with future planning. Principals are told that the randomization information must remain confidential until completion of baseline data collection in the fall.

The project’s measurement coordinator trains staff according to standardized protocols and certifies each one for data collection only after successful practice demonstrations. The measurement coordinator or project manager oversees all sessions to ensure fidelity to the measurement protocol. The same group of trained staff collects data for each cohort or matched pair including an intervention and control school over the same three- or four-week period. Only half of the data is collected from half of the girls at each paired school during the first week. The remainder of the data is collected from the same wave of girls during either the second or third week. Half of the data is obtained from the other half or wave of girls at each school during the second or third week with the remaining half of the data being collected during the following week (week three or four, respectively). Whether the data collection spans across three or four weeks for each pair of schools is determined based on requests from school administrators. To reduce the potential of non-typical PA occurring during a single week for all girls at a particular school site, two waves are used during all data collection periods in every participating school. Obtaining half of the data, as opposed to all, at a single time point also reduces the response burden for the girls and decreases the time needed during a school day. Complete data are collected at pre-intervention/baseline and immediately post-intervention (after 17 weeks). At 9-month post-intervention F/U, only PA is measured (via accelerometer) to assess for any long-term effects. For completing the survey data at each time period, girls receive an incentive, such as a T-shirt or a drawstring backpack, with the Girls on the Move logo. For wearing the accelerometer as instructed for one week at each time period, girls receive a $20.00 gift card to a local general store. If the data are inadequate due to limited wear-time and the accelerometer needs to be re-worn, girls receive a reduced gift card amount of $10.00 after the second week of wearing it.

After all baseline measures are obtained in a school, members of the research team contact the parents and girls by phone to inform them of their school’s randomization status. The measurement and intervention teams function independently so as to blind members of the former group to each school’s randomization status throughout the entire study. Girls, parents/guardians, principals, nurses, and school staff are not told about hypotheses.

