#### Data analysis

Data will be analyzed using SAS 9.3 (SAS Institute Inc., Cary, NC) [72]. Outcome measures include the primary outcome: minutes of MVPA; secondary outcomes: CV fitness, BMI, and percent body fat; and mediating cognitive and affective variables. Potential covariates measured at baseline are personal factors and behaviors. To adjust for non-independence of observations within each school and the dependence within person, analyses below will be carried out using a multilevel model approach frequently used in group randomized trials [73] that will incorporate baseline measures as covariates [74,75]. Multilevel generalized linear models [73,76] will be fit for ordinal, and discrete outcomes using appropriate link functions. Assumptions of normality for continuous outcome variables will be evaluated; normalizing transformations or generalized linear mixed effect models will be used if warranted [76].

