#### Primary analyses

Primary analysis is of intention to treat type [78,79], which gives a conservative estimate of treatment effect compared with what would be expected if there was full compliance [80]. Effect sizes and their confidence intervals (adjusted for baseline values of outcomes and nested study design) will be computed. Variance components (school and participants) will be estimated.

We will use: Statistical Model #1: Outcome (after 17 weeks) = outcome (baseline) + study group + covariates. The essential parameter tested in this model is the coefficient for the study group variable. Covariates will be included if preliminary analyses reveal group differences at baseline despite randomization. We will model 9-month post-intervention F/U MVPA, controlling for MVPA after 17 weeks (immediately post-intervention): MVPA (9-month post-intervention F/U) = MVPA (after 17 weeks) + study group + covariates.

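### Schools are matched in pairs and split evenly by year, but the stated model has no pair or year term, so the standard error takes no credit for the pairing

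*Protocol article*

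**What the plan says.** Design (Protocol article, Study design). In each of three years eight schools are randomised, four to each arm. Before that, "schools are paired prior to randomization based on the following criteria": school type, size, racial mix and the proportion on free or reduced-price lunch. The section then describes a "matched pair including an intervention and control school", and says that "The same group of trained staff collects data for each cohort or matched pair" "over the same three- or four-week period". Read together, these statements imply randomisation within 12 pairs, although no sentence says so outright.

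Analysis (Data analysis; Primary analyses). The multilevel model is introduced "To adjust for non-independence of observations within each school and the dependence within person". Model #1 is "Outcome (after 17 weeks) = outcome (baseline) + study group + covariates", and "Variance components (school and participants) will be estimated". The 9-month model has the same form. Covariates are drawn from personal factors and behaviours and enter only if the groups differ at baseline. Neither pair nor study year appears in the clustering levels, the variance components, the model equations or the power calculation.

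**The concern.** The two schools of a pair resemble each other by selection and are measured in the same weeks, so they share season, weather and school calendar. If that similarity carries into minutes of MVPA, the difference between arms varies less than two independent sets of 12 schools would suggest. A model with only a school level cannot see this. It leaves the shared pair variance in the between-school variance that forms the error term for the group effect.

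The standard error is then larger than the design warrants, and real precision goes unreported. With 24 schools this matters, because power rests mainly on the number of schools. It is more than detail left for a later document: the article itself sets out the levels, the variance components, the equations and the covariate rule, and pair is absent from all of them.

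**Working it through.** **Inputs** (Power calculations): effect 0.20 = 16 min/week on an SD of 80; ICC 0.02; 12 schools per arm; 50 girls per school; two-sided alpha 0.05. **Assumption:** the pair explains a share f of the between-school variance. The protocol does not give f, so a range is shown.

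**The plan's own figure.** Design effect = 1 + 49 × 0.02 = 1.98. Effective n per arm = 600 / 1.98 = 303. SE = 80 × √(2/303) = 6.50 min. 16 / 6.50 = 2.46. Power is 0.69 on the normal approximation and 0.65 on t with 22 df. The stated .80 is not reproduced from these inputs. That is a separate point, and a baseline R² of about 0.23, which is not stated, would close the gap.

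**Effect of ignoring the pairs** (unadjusted school means).

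- Variance of a school mean, in SD² units: 0.02 + 0.98/50 = 0.0396.
- Unpaired SE = 80 × √(2 × 0.0396/12) = 6.50 min, whatever f is.
- Correlation of school means within a pair: ρ = f × 0.02/0.0396 = 0.505f.
- True SE of the arm difference = 6.50 × √(1 − ρ).
- 95% half-width: unpaired 2.074 × 6.50 = 13.5 min (22 df); paired 2.201 × true SE (11 df).

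Type I error and power of the unpaired test come from simulation of at least 200,000 trials per setting. Paired power comes from the noncentral t on 11 df.

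| f | ρ | True SE (min) | Unpaired SE too large by | Paired half-width (min) | Type I error, unpaired | Power, unpaired | Power, paired |
|---|---|---|---|---|---|---|---|
| 0 | 0 | 6.50 | 0% | 14.3 | 0.050 | 0.65 | 0.61 |
| 0.25 | 0.126 | 6.08 | 7% | 13.4 | 0.037 | 0.66 | 0.67 |
| 0.50 | 0.253 | 5.62 | 16% | 12.4 | 0.026 | 0.67 | 0.74 |
| 0.75 | 0.379 | 5.12 | 27% | 11.3 | 0.016 | 0.69 | 0.81 |

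**Break-even.** The paired interval is narrower when √(1 − ρ) < 2.074/2.201, that is ρ > 0.112, or f > 0.112/0.505 = 0.22.

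**Year.** In the unpaired model a three-level year effect moves the error df from 22 to 20, and power from 0.653 to 0.649.

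**Random pair effect with adaptive df.** If a pair variance estimated at zero drops the pair and restores 22 df, type I error is 0.063 at f = 0 and about 0.057 at f = 0.25. At f = 0 the estimate is zero in about half of trials. Keeping 11 df but still using the pooled unpaired SE in those trials gives 0.057 at f = 0 (400,000 simulations). Keeping the within-pair SE as well gives 0.050.

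**The case against.** A reader might infer that the pairing gains nothing, or that the planned interval is simply too wide. The documents support neither. The stated purpose of pairing is to avoid bias, and balance survives an unpaired analysis. Pairing also lowers the true variance of the estimate, which is why unpaired power rises from 0.65 to 0.69 down the table. The excess width depends on a correlation that the protocol does not give; below f of about 0.22 the paired interval is the wider one. Breaking the matches to keep 22 df is a defensible choice with 12 pairs, and the test stays valid.

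Other objections also carry weight:

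- Model #1 adjusts for baseline MVPA, measured under the same paired arrangement, so stable pair differences would be partly absorbed. Effects of the particular post-intervention weeks would not be.
- Girl-level grade, race or ethnicity and lunch-programme status are collected as personal factors and are candidate covariates. But they enter only if the arms differ at baseline, which matching makes less likely.
- The staff sentence reads "The same group of trained staff collects data for each cohort or matched pair including an intervention and control school", so a team may serve a whole cohort, and an accelerometer leaves little room for measurer effects. Shared weeks are the stronger argument.
- The equation is schematic and omits the school effect too. The variance-component sentence, however, lists its levels and does not include pair.

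These points limit the size of the concern. None of them shows that the analysis accounts for the pairs or that ignoring them was deliberate.

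**Conclusion.** The mismatch between design and stated analysis is real, and its cost is conditional. If paired schools are alike, the planned test is conservative: with half of the between-school variance shared by pairs, the SE is 16% too large, type I error is 0.026, and power is 0.67 against 0.74. The 95% interval is 13.5 min either side against 12.4, a narrowing of 8% once the lost df are counted. If pairing explains nothing, the planned analysis is the better one by about 4 points of power.

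These figures rest on the protocol's ICC and cluster size, an assumed f, unadjusted school means, and the inference that randomisation was within pairs. Baseline adjustment would probably shrink them. The error runs in the safe direction, so it should be corrected but does not threaten the trial's validity.

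**What to change.** In Model #1 and in the 9-month model:

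1. Add study year as a fixed effect. It uses 2 df at negligible cost.
2. Account for the matched pair, with school nested in pair.
3. Fix the degrees of freedom for the group effect in advance at the pair level (about 11), and keep them even if the pair variance is estimated at zero. Take the SE from within-pair differences in that case too, for example by leaving the pair variance unbounded.
4. Report the pair variance component beside those for school and participant.

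Settle this before outcome data are examined by arm. It needs no new data. The price is about 4 points of power (0.65 to 0.61) if pairing explains nothing. If the team prefers to break the matches and keep the larger df, the plan should say so and give the reason, with year retained.

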#### PA club evaluation

PA club instructors use the Internet-based program to record reach (e.g., girl’s attendance and punctuality at PA club). To assist the researchers in evaluating dose, one of the PA club staff members serving as the club manager records the types of activities offered for the day, including whether healthy snacks were distributed.

The second author trained four process evaluators to evaluate the PA club via an observation tool and a quantitative checklist with rating scale in the first mo. (week 3), at the midpoint (week 9), and near the end (week 15). The checklist includes items for evaluating dose delivered or staff adherence to specific areas associated with the PA club protocol and fidelity or the degree that the PA club reflects important theoretical concepts of the HPM (e.g., enjoyment - “fun” PAs offered) and SDT (e.g., autonomy, relatedness, competence). A process evaluator evaluates the entire session for one day during one week, and another process evaluator evaluates the session on another day during the same week. They report to the second author at the end of each week and discuss their findings. The second author or intervention coordinator intervenes as needed with the PA club instructors to promote interventionist consistency in adhering to the protocol.

Five girls per school are randomly selected every other week to wear the ActiGraph GT3X-plus to measure the girls’ level of PA during the club time. To determine dose received, data are downloaded at the end of each week to a computer. A research team member (e.g., intervention coordinator, project manager, principal investigator, co-investigator) randomly monitors a session at each club at least weekly to evaluate adherence to protocols and retrain staff as needed. During the middle of the first half of the intervention, the manager contacts parents/guardians of all girls who missed a week (all 3 days) or more than an average of two PA club sessions in a week over the initial three 3-week period to explore ways to help the girls attend the club and attain adequate PA.

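### Measurement is described as run by a blinded, independent team, yet the project manager, who knows every school's allocation before baseline, may oversee measurement sessions

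*Protocol article*

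**What the plan says.** The blinding claim closes the Study design section of the protocol article: "The measurement and intervention teams function independently so as to blind members of the former group" to each school's "randomization status throughout the entire study". It has two linked parts. The teams are separate, and that separation is the means by which the measurement team stays unaware of allocation.

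Three other statements concern the project manager:

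- Study design, on telling schools their allocation: "Prior to the start of the school year, the PI and project manager inform each principal regarding the randomization status".
- Study design, on quality control of data collection: "The measurement coordinator or project manager oversees all sessions to ensure fidelity to the measurement protocol".
- PA club evaluation, on monitoring of the after-school clubs: "A research team member (e.g., intervention coordinator, project manager, principal investigator, co-investigator) randomly monitors a session at each club at least weekly". The monitor also retrains club staff when that is needed.

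Study design adds, on who takes the measurements: "The same group of trained staff collects data for each cohort or matched pair including an intervention and control school".

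**The concern.** One role appears on both sides of a separation that the article presents as the safeguard for its outcome measurement. The project manager holds the allocation of every school before any baseline data are taken, and may then supervise the sessions at which outcomes are collected.

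Two things are at stake. The first is a route for bias. The overseer may disclose the arm, even inadvertently, to staff who are meant to be unaware of it, or may supervise the two schools of a pair differently. Some steps depend on how staff conduct them: a staff member gives and reviews the accelerometer wear instructions, and staff record PACER laps. Wear matters to the primary outcome because only girls with at least four days of data are to be analysed.

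The second is the accuracy of the report. The trial commits itself to CONSORT reporting. A statement that measurement was blinded and independent should say whom it covers.

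**Working it through.** No arithmetic applies: the point does not depend on alpha, power, effect size or sample size. The check is whether the roles given to the project manager are compatible with the claim.

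| Question | What the article says | Section |
|---|---|---|
| Is blinding of the measurement team claimed, and for how long? | Yes, for the entire study | Study design |
| How is it secured? | By keeping the measurement and intervention teams independent | Study design |
| Does the project manager know allocation? | Yes, for each school, before the school year | Study design |
| Does the project manager have a role in measurement? | Yes, as an alternative to the measurement coordinator in overseeing all sessions | Study design |
| Does the project manager have a role in the intervention? | Possibly: one of four examples of who may monitor clubs | PA club evaluation |
| Is the oversight limited by time point, school or arm? | No limit is given | – |

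Step by step:

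1. **Timing.** Principals are told before the school year and must keep the information confidential until baseline collection in the fall is complete. The project manager, who tells them, is therefore unblinded before baseline.
2. **Reach.** The oversight sentence covers all sessions and names either role. Measurement takes place at both schools of every pair, so the sessions open to this oversight lie in both arms.
3. **Conflict.** An overseer who knows the allocation is present in the process that independence is meant to protect. In those sessions the separation does not hold. The three Study design statements are enough to show this.
4. **Club monitoring.** Clubs run only in intervention schools. If the project manager is the one who monitors them, the same person has a hand in intervention fidelity and in measurement. The list is introduced by e.g., so this is a possibility that strengthens step 3. Step 3 does not need it.
5. **Extent.** The word or in the oversight sentence leaves the share of sessions overseen by the project manager anywhere from none to all. The article gives no figure.

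**The case against.** The strongest reply is that the contradiction is not literal. The claim protects members of the measurement team, and the project manager is nowhere placed on that team. Study design distinguishes the trained and certified staff who collect data from the person who oversees them. Blinded collectors and an unblinded overseer can coexist. This stands, and it limits the point. A reader might infer that any published claim of blinded measurement would be untrue; the document does not support that, because the claim may still be true of those who take the measurements. What the reply does not rescue is the stated independence of the teams.

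The second reply is that the outcomes are well protected:

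- MVPA comes from accelerometer counts with fixed thresholds and stated wear rules. Wear instruction includes a video, and reminders are automated calls.
- Re-wear is tied to inadequate wear time and is not described as the project manager's choice.
- PACER is paced by audio cues and has a stopping rule. No staff encouragement is described.
- Surveys are taken on an iPad with voiceover. Weight and percent body fat are read from a scale.
- The same staff measure both schools of a pair over the same weeks, which limits differences between arms.

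Most of this stands too. One might infer that an unblinded overseer can influence every outcome; that is not shown. A narrower route remains through the steps that staff run in person, and shared staff also mean that a disclosure would reach the people measuring both schools.

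Three further inferences should be resisted. The project manager cannot be said to monitor the clubs as a matter of fact, since the role is only an example in a list. The project manager's scheduling of recruitment meetings, described under Participants, eligibility, and recruitment, is not outcome measurement and does not bear on this claim. No statement puts the principal investigator or the intervention coordinator in measurement sessions, so there is no ground here for barring them.

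**Conclusion.** The point holds in a limited form. The article claims a separation of teams that its own assignment of roles does not secure: in any measurement session overseen by the project manager, a person who knows the allocation is supervising outcome collection. Allocation could pass to the data collectors or affect staff-run steps, chiefly accelerometer wear instructions and PACER lap recording.

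The size of any bias cannot be derived from the document. Neither the share of sessions concerned nor any effect of oversight on wear or laps is given. The trial's target difference is small, at 0.20 × 80 = 16 minutes of MVPA per week, but that says nothing about how large a bias might be. The instrument-read outcomes are less exposed than the steps that staff conduct.

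The conclusion assumes that no safeguard in a fuller document masks or restricts the project manager's oversight; the article states none. It does not assume that the data collectors are in fact unblinded. The matter should be corrected because the remedy is cheap and the blinding claim is likely to be carried into the trial report.

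**What to change.** Change the oversight sentence under Study design so that measurement sessions are overseen only by the measurement coordinator or by another existing, certified member of the measurement team who is unaware of allocation. This assumes that the coordinator is covered by the blinding claim; the revised sentence should say so.

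If that cover cannot be arranged, keep the project manager as an alternative, state plainly that this role is unblinded, and limit the blinding claim to the staff who collect the data.

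The first option costs slightly less flexible cover for sessions and some reassignment among existing staff. The second costs only a narrower claim, and it leaves the route for bias in place. Neither changes the sample size, outcomes or analysis.
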